## Background

The prevalence of symptomatic heart failure (HF) is rapidly growing due to the aging of the population, successful treatment of myocardial infarction, and increased survival after an acute cardiac event [1,2]. The more frequent need for rehospitalisations and poorer survival chances in the chronic HF population are associated with major healthcare costs. For instance, almost 390 million Euros were spent on HF care in the Netherlands in 2005, and it is expected that these costs increase during the following decades [3].

Pharmacological treatment of HF typically consists of a combination of ≥4 different types of medication [4]. A major problem in HF management is poor medication adherence with rates varying from 10% to 99% [5]. Poor adherence to treatment may to a great extent explain frequent readmissions in HF patients [5], and is associated with increased morbidity and mortality [6]. A recent longitudinal study showed that medication adherence rates above 88% were associated with a reduced number of rehospitalisations and mortality rates compared to non-adherent patients [7]. In this study, objective medication adherence was measured using an electronic chip in the medication cap (*"Medication Event Monitoring"*) that records each moment the cap is removed from the medication bottle [7]. Hence, improving medication adherence may enhance cardiac prognosis, reduce the number of HF-related hospital readmissions, improve quality of life (QoL), increase survival, and reduce healthcare costs [8].

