### Study endpoints

The main study parameters include objective and subjective medication adherence, number of hospitalizations, healthcare consumption and costs (see Table 1). Objective medication adherence will be assessed using the monitor output collected in a web-based application (CarebyWeb), and the prescription refill records provided by the patients' pharmacies. A cost-benefit analysis will be assessed by means of the TiC-P questionnaire[20] and event rate (and related DBC (diagnosis treatment combination, the Dutch system to allocate costs to treatments of specific patient groups)). The TiC-P questionnaire will enable us to compare healthcare consumption in the intervention and control group.

**Table 1 T1:** Measures & design

Construct/Measure	Methods of assessment	T0 Pre	T1 Post	T2	T3	T4	T5
*Primary outcomes*							
Adherence	Objective: Monitor output	X	X				
	Refill rate pharmacy	MR	MR		MR		MR
	Subjective: MAS, MOS-adhere	Q	Q	T	Q	T	Q
Healthcare Consumption	Number of rehospitalisations, time to first HF-related hospitalization, visits to the GP and ER due to cardiac causes, DBC codes	MR	MR	MR	MR	MR	MR
	TiC-P,	Q	Q	T	Q	T	Q
*Secondary outcomes*							
Physical function,	6-minute walk test	A	A		A		A
disease progression	NYHA, LVEF	S	S		S		S
Quality of life	KCCQ	Q	Q		Q		Q
*Predictors*							
Sociodemographic	Self-report, postal code area	Q					
Self-care behavior	EHFScBS-9	Q	Q		Q		Q
Cognitive function	MMSE	A	A		A		A
Depression	PHQ9, BDI10	Q	Q		Q		Q
Anxiety	GAD7, SAD4	Q	Q		Q		Q
Type D personality	DS14	Q	Q				

NB. Multiple instruments are used to assess anxiety and depression since there is no gold standard or consensus which instruments to use in patients with somatic disease. All psychological questionnaires are standardized and validated. Variables obtained from: S = standard measures in routine clinical care visits, A = additional assessment physical/cognitive functioning, MR = medical records, Q = questionnaire, X = intervention, T = telephone call.

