### Statistical analysis

This trial is designed to show whether the MASS device is effective in improving medication adherence in a chronic HF population compared to usual care only. Descriptive statistics (frequencies, means (±SD) will be calculated stratified by experimental group (intervention vs. usual care). T-tests for continuous variables and Chi-square tests for categorical variables will enable us to compare baseline values for both groups to formally test the successfulness of the randomization procedure. We will examine the effectiveness of the intervention by using the intention-to-treat principle, with the inclusion of all randomized participants in the statistical analyses regardless of whether they completed the intervention or the follow-up measurements. Missing data will be imputed using regression imputation techniques. The equality of subjective and objective adherence will be assessed by means of Intraclass correlation and Cohen's measure for agreement, the Kappa statistic, depending on the measure of adherence. Repeated measures analysis of covariance will be used to assess differences between the intervention and control group with respect to changes in adherence over the six-month intervention period, and to assess long-term effects (up to one year post-intervention) of the intervention on medication adherence, while taking potential confounders into account. To determine whether the time to hospitalization is longer for patients using the MASS device compared with patients in the control group, the log-rank test for comparison of Kaplan-Meier curves will be used. In addition, Cox proportional hazards regression modeling will be used to determine whether the usage of the MASS device predicts time to the first event (i.e. hospitalization due to HF or cardiac-related death). Multivariate regression analyses will be used to assess which psychological, clinical, demographic, and/or medication-related determinants predict adherence (with the percentage of adherence as dependent variable) in chronic HF patients and moderate the effects of the MASS device on patient adherence. The influence of potential effect modifiers will be examined by means of interaction terms.

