## Discussion

The TELEMED-HF study is designed to test the efficacy and cost-efficiency of an innovative telemonitoring solution, the MASS device, in improving medication adherence as compared to usual care alone in a large group of HF patients. Currently, a few major clinical trials have used strategies consisting of daily telemonitoring of symptoms and health behaviors in HF patients [13,14]. However, the TELEMED-HF study is the first trial that primarily focuses on improving medication adherence by recording adherence, dispensing all prescribed medication in the right dosage at the specified times, reminding patients to take their medicines, and collecting information about non-adherence from the MASS device and responding to it. While we have chosen for a commercially available telemonitoring device, the study is designed to test its concept rather than the product itself, resembling the Tele-HF study that investigated a commercially available system on health behaviors in HF patients [23].

As the MASS device is expected to train adherent behavior, it can be considered as a behavior-based intervention. To date, most studies did not examine the effect of telemonitoring on longer term outcomes past 6 months, nor the clinical course of HF [12]. This RCT is therefore designed to determine the effect of medication adherence on the clinical state, disease progression, health care consumption, and QoL with a follow-up period of one year. We will further examine the correspondence between objectively and subjectively assessed medication adherence. Finally, our aim is to identify psychosocial and clinical determinants of medication adherence, and their role in modulating adherence and the effect of the telemonitoring device.

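### An intraclass correlation between questionnaire scores and a refill rate or monitor output, with no common unit stated, would reflect the scoring range and the form of coefficient more than agreement

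*Protocol article*

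**What the plan says.** The Statistical analysis section states: "The equality of subjective and objective adherence will be assessed by means of Intraclass correlation". The same sentence adds a second statistic, "Cohen's measure for agreement, the Kappa statistic, depending on the measure of adherence". It does not say which measure goes with which statistic.

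Table 1 (Study endpoints) lists the inputs. The self-report row reads "Subjective: MAS, MOS-adhere". The objective row begins "Objective: Monitor output" and continues with the pharmacy refill rate, which the text above the table describes as "the prescription refill records provided by the patients' pharmacies". Monitor output is marked at T0 and T1 with the code for the intervention. Refill rate is listed at T0, T1, T3 and T5.

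A percentage appears later in the Statistical analysis section, where the determinants regression is to be run "with the percentage of adherence as dependent variable". The Discussion commits to the comparison: "We will further examine the correspondence between objectively and subjectively assessed medication adherence".

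The article gives no score range, direction or rescaling for either questionnaire, no form of the intraclass correlation and no cut-off for kappa.

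**The concern.** An intraclass correlation answers whether two readings of the same quantity, in the same unit, coincide. In its absolute-agreement form, which is what a test of equality implies, any difference in mean or SD between the two readings lowers the coefficient. The consistency form forgives a difference in mean but still penalises a difference in SD.

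A questionnaire total and a share of medication refilled or dispensed have no stated unit in common. Equality between them is then undefined, and the coefficient depends on how many points the questionnaire has and on which form the software computes. Kappa covers categorical comparisons. For continuous pairs the sentence leaves the intraclass correlation, and that is where it does not fit.

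At stake is the conclusion on whether self-report reflects actual adherence. Both kinds of measure are listed as primary outcomes, so a coefficient that is low because of scaling could wrongly discredit one of them.

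**Working it through.** The article states no agreement coefficient, target or precision, so there is no figure to reproduce. The check asks what the planned statistic returns when the two measures track each other perfectly.

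**Inputs.** All are assumptions except the sample size of 400, which is taken from the Statistical power analysis section. The percentage has mean m1 and SD s1. The score is an exact linear function of the percentage on a range lo to hi, so r = 1, m2 = lo + (hi − lo) × m1/100 and s2 = (hi − lo) × s1/100. The 88% in the Background ("medication adherence rates above 88% were associated with a reduced number of rehospitalisations") is a threshold from a cited study, not an expected mean. Means from 70 to 88 and SDs from 10 to 20 are therefore assumed.

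**Formulas** (two measures, r = 1, large sample, D = m1 − m2):

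- absolute agreement ≈ 2·s1·s2 / (s1² + s2² + D²)
- consistency = 2·s1·s2 / (s1² + s2²)
- one-way ≈ (4·s1·s2 − D²) / (2·s1² + 2·s2² + D²)

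**By hand, percentage 85 (SD 12):**

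- Range 0-4: score 3.4 (SD 0.48). Absolute agreement = 11.52 / (144.2 + 6658.6) = 0.002. Consistency = 11.52 / 144.2 = 0.080. One-way = (23.0 − 6658.6) / (288.5 + 6658.6) = −0.955.
- Range 5-25: score 22 (SD 2.4). Absolute agreement = 57.6 / (149.8 + 3969) = 0.014. Consistency = 57.6 / 149.8 = 0.385.

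**By simulation**, from ANOVA mean squares, n = 400, percentages clipped to 0-100, with mean/SD of 88/10, 80/15 and 70/20. Each cell gives the span over the three pairs, and r = 1 throughout:

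| Assumed score range | Absolute agreement | Consistency | One-way |
|---|---|---|---|
| 0-4 | 0.001 to 0.006 | 0.080 | −0.979 to −0.846 |
| 0-8 | 0.002 to 0.013 | 0.159 | −0.975 to −0.822 |
| 5-25 | 0.007 to 0.050 | 0.385 | −0.953 to −0.681 |
| 6-36 | 0.014 to 0.100 | 0.550 | −0.925 to −0.524 |
| 0-50 | 0.035 to 0.221 | 0.800 | −0.848 to −0.221 |
| 0-100, same unit | 1.000 | 1.000 | 1.000 |

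The data in every row carry the same information. Only the scoring range and the form of the coefficient change, and the unrescaled results run from −0.98 to 0.80.

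**What rescaling does.** With the score placed on 0-100 and its mean and SD equal to those of the percentage, all three forms return 1.000. A common range does not guarantee that match. With an assumed rescaled score of 92 (SD 8) against 85 (SD 12) and r = 1, absolute agreement = 192 / (144 + 64 + 49) = 192 / 257 = 0.75.

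**What the alternatives do.** On the same perfectly tracking data the Pearson correlation is 1.000 on every range. Kappa at matching cut-offs, checked on the 0-4 score, is 1.000.

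**Why the form must be named even within one unit.** For two percentages that differ by a constant 10 points, absolute agreement is 0.582, 0.812 and 0.879 for the three mean/SD pairs, while consistency is 1.000 each time.

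**The case against.** The strongest reply is that the article never says raw scores will be set against a percentage. It gives no scoring for the questionnaires. Its objectives name determinants of both subjective and objective adherence, and the regression for those determinants uses a percentage, so subjective adherence might also be expressed as one. The power calculation assumes an SD of 1 for adherence, which is compatible with standardised scores. Kappa is planned beside the intraclass correlation. Scoring, harmonisation, form of coefficient and cut-offs are details that a journal article may leave to the full protocol or analysis plan.

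Much of this stands. A reader might infer that the trial is bound to report almost no agreement whatever the data. The documents do not support that: raw entry and the ranges are assumptions, the form is unstated, consistency reaches 0.80 on a 0-50 range, and part of the comparison may go to kappa. A reader might also infer that the trial's main result is threatened. It is not: the comparison is absent from the Study objectives section and is not a comparison of arms.

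What the reply does not remove is the mismatch between the statistic that the article does name and the inputs that it does list. Neither the regression phrase nor the SD of 1 says how a questionnaire score becomes a percentage. Rescaling supplies a common range, but 80 on a rescaled questionnaire is not 80% of doses taken.

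**Conclusion.** The point holds in a limited form. For continuous pairs of questionnaire score and refill rate or monitor output, the intraclass correlation is ill suited to the stated purpose, and no common unit is given that would make it suitable. If scores are entered in their own units, perfectly tracking measures give absolute agreement of about 0.00 to 0.05 on ranges from 0-4 to 5-25 and at most 0.22 on 0-50, consistency of 0.08 to 0.80, and a negative one-way coefficient. These figures rest on assumed ranges, means and SDs and on a linear relation with r = 1. They show how far the coefficient depends on scaling and do not predict what the trial would find. The consequence is a possible wrong statement about the value of self-report in a supporting analysis. The comparison of the intervention with usual care is not affected.

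**What to change.** Replace the agreement sentence in the Statistical analysis section with three parts:

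1. Questionnaire score against refill percentage, and against monitor percentage in the intervention arm: Spearman rank correlation with 95% CI, described as association and not as equality.
2. Agreement: kappa with percent agreement beside it, only on adherent/non-adherent classifications whose cut-offs are fixed in advance for both measures. The 88% in the Background comes from a study of electronic bottle-cap openings, so carrying it over to refill data would need its own justification.
3. Intraclass correlation: keep it, with the absolute-agreement form named, only for pairs in the same unit over the same period, such as monitor percentage against refill percentage in the intervention arm. This compares two objective measures and does not answer the self-report question.

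The cost is one rewritten sentence, with no new data, visits or patients. There is a small downside: a rank correlation shows association only, so the judgement on agreement then rests on the kappa.

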### Study procedures, randomization, and follow-up

The study protocol has been approved by the medical ethics committee of the TweeSteden Hospital as well as by the local regulatory authority of the TweeSteden Hospital. The trial conforms to the principles most recently outlined in the Declaration of Helsinki (2008). All patients will be informed orally and in writing about the purpose, rights, and possible benefits/risks of the study prior to participation. We have guaranteed full participation of the HF outpatient clinic of the TweeSteden hospital. Eligible patients will be invited to participate in the study during a regular visit to the HF nurse or cardiologist at the HF outpatient clinic. After 4 to 7 days patients will be contacted by telephone and asked for participation. Positively responding patients will then sign the informed consent forms and receive an appointment at the HF outpatient clinic within two weeks for their baseline visit (T0).

Patients will be randomly assigned following a blocked randomization procedure (computerized random numbers) to either the intervention arm or to usual care (1:1). Due to the restriction of a limited number of MASS devices at our disposal, the randomization procedure will be performed per week so that each week a maximum of 6 patients is assigned to either condition arms. In order to prevent selection bias, the allocation sequence will be concealed from the researcher and the HF nurse enrolling and assessing patients in sequentially numbered, opaque, and sealed envelopes. A second researcher working outside the hospital will develop and monitor the concealment system.

All patients will visit their HF nurse for their first usual care visit (T0). Corresponding envelopes based on the order of inclusion sequence will be opened only after completion of all baseline assessments during this visit to allocate the intervention. If the patient has been randomized to the intervention group, he/she will receive the MASS device and instructions, and will be fully explained how to use it. The intervention period starts within two weeks after this visit, for a period of 6 months (see below for specific details on intervention).

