**Figure 1 F1:**
[figure not shown]
**Timeline study procedure**. The figure shows a timeline of the study procedure.

Over the 18-month study period as well as the year before inclusion, retrospective refill rates will be requested from the patients' pharmacies. The general practitioner of the patients will be informed of the patients' participation in the study and will be asked to report the total number of patient visits to their clinic by filling out a patient contact form sent by us every 6 months.

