### Statistical power analysis

The most demanding analysis in this trial with regard to statistical power and sample size is the survival analysis in which adherence is a predictor of the number of HF-related hospitalizations. A power analysis in PASS for a Cox proportional hazard regression model [21] was performed, using information from the TweeSteden hospital and previous studies. Assuming an event rate of 29% (data 2008 and 2009, TweeSteden hospital), an estimated hazard ratio of between .70 and .80 [6], taking into account an SD of 1 for our main predictor adherence, and a correlation with covariating factors of on average .30, a two-sided type I error of .05, and a minimal power of 80% to detect a HR of .70, the sample size needed for this study to be sufficiently powered is 400. In an earlier study conducted at the same outpatient clinic and within the same patient population, a response rate of 78.3% was shown with a 19.9% attrition rate [22]. Thus, in order to achieve the calculated sample size of 400 patients, we intend to include 480 patients at baseline (1:1). Based on a more conservative response rate of 70%, 685 patients need to be approached. With 400 patients visiting the outpatient clinic each year (approximately 3-5 new patients/week) inclusion of such a number within two years is feasible. This sample size is also sufficient to test the other, less power demanding, research questions.

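### The adherence comparison is framed on change from baseline and does not name T0 adherence as a covariate; naming it would gain precision at almost no cost

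*Protocol article*

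**What the plan says.** The Statistical analysis section of the Protocol article gives the model: a repeated measures analysis of covariance is to be "used to assess differences between the intervention and control group with respect to changes in adherence over the six-month intervention period". The same model is to assess long-term "effects (up to one year post-intervention) of the intervention on medication adherence, while taking potential confounders into account". The confounders are not listed, and T0 adherence is neither named as a covariate nor ruled out.

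Baseline adherence is available for three measures. On refill, the text under Figure 1 says: "Over the 18-month study period as well as the year before inclusion, retrospective refill rates will be requested from the patients' pharmacies". Table 1 places refill rate at T0, T1, T3 and T5, and the row "Subjective: MAS, MOS-adhere" at every occasion from T0 to T5. Under Study procedures, the allocation envelope is opened only after all baseline assessments are complete, so the T0 values precede allocation.

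Monitor output is different. The same section says: "If the patient has been randomized to the intervention group, he/she will receive the MASS device and instructions". No device use is described for usual care.

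The Statistical power analysis section sets "a two-sided type I error of .05, and a minimal power of 80% to detect a HR of .70" for a Cox model. For the adherence comparison it gives no effect size, SD or correlation between baseline and follow-up, only a general assurance that the sample size is sufficient.

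**The concern.** The Statistical analysis section opens by saying that the trial is designed to show whether the device improves adherence, so this comparison carries the main efficacy question. Within the six-month intervention period, Table 1 has only two occasions for refill and questionnaire adherence, T0 and T1. A repeated measures analysis of change over those two occasions, with T0 as one of the repeated levels, tests the arm-by-time interaction. That test is the same as a two-sample test on T1 minus T0.

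Other parts of the article point the same way. Table 1 places T0 adherence under primary outcomes and not under predictors. The list of moderating and randomisation-check variables in Study endpoints does not contain it either.

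At stake is precision. A change score subtracts the whole baseline value, whereas a covariate model subtracts only the part that predicts follow-up. The planned wording may therefore give wider confidence intervals than the same patients and visits could deliver.

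**Working it through.** **Inputs.** From the article: 200 per arm, and two-sided alpha 0.05 (stated for the Cox model and borrowed here). Assumed, because the article gives no value: the T0-T1 correlation rho, equal SDs at T0 and T1 (set to 1), and the effect size. The article states no power figure for adherence, so there is none to reproduce; the sample size of 400 comes from the Cox model and does not bear on this point.

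**Step 1: variances.** Per patient, in units of the outcome variance:
- change score: 2(1 - rho)
- T1 adjusted for T0: 1 - rho²
- ratio, adjusted to change: (1 - rho²) / [2(1 - rho)] = (1 + rho)/2

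The ratio is below 1 for every rho below 1.

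**Step 2: power.** With 1.960 + 0.842 = 2.802:
- if the change analysis has 80% power, the adjusted analysis has Phi[2.802/√ratio - 1.960]
- if the adjusted analysis has 80% power, the change analysis has Phi[2.802 × √ratio - 1.960]

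| Assumed rho | Variance ratio | Adjusted power if change has 80% | Change power if adjusted has 80% |
|---|---|---|---|
| 0.3 | 0.65 | 93.5% | 61.7% |
| 0.5 | 0.75 | 89.9% | 67.9% |
| 0.7 | 0.85 | 86.0% | 73.3% |
| 0.8 | 0.90 | 84.0% | 75.7% |
| 0.9 | 0.95 | 82.0% | 78.0% |

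Example at rho = 0.5: 2.802/√0.75 = 3.235; 3.235 - 1.960 = 1.275; Phi(1.275) = 0.899. A simulation of 4,000 trials with 200 per arm agrees: change against adjusted 79% and 93% (rho 0.3), 80% and 89% (rho 0.5), 80% and 86% (rho 0.7).

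**Step 3: other scales at rho = 0.5.** The smallest effect detectable with 80% power and 200 per arm is 2.802 × √(2/200) = 0.28 SD for change and 0.28 × √0.75 = 0.24 SD with adjustment. Equivalently, 200 × 0.75 = 150 per arm with adjustment would match 200 per arm without it.

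**Step 4: a large effect.** At 0.5 SD and 200 per arm, power for change and adjusted analyses is 98.8% and 99.9% at rho 0.3, and 99.9% and 100.0% at rho 0.5. The gain is then about 1 point or less.

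**Step 5: does the word change settle it?** No. If T1 = a + b·T0 + d·arm + error, then T1 - T0 = a + (b - 1)·T0 + d·arm + error. The arm effect d and its error are identical. Change analysed with T0 as a covariate therefore loses nothing; the loss arises only when T0 is a repeated level and not also a covariate.

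These figures are for the T0-T1 contrast. No power is calculated for a joint test over all visits to T5.

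**The case against.** The strongest reply is that the method is called analysis of covariance, its covariates are unlisted, and T0 adherence may be among them. A condensed article may leave the covariate list to the analysis plan. If T0 adherence was meant, the loss is zero and only the wording needs attention. This stands as far as it goes: a reader might infer that baseline adherence is definitely left unadjusted, and the article does not say that. But the article already fixes the quantity compared as change, places T0 adherence among the outcomes, and mentions only confounders as covariates. In a randomised trial, a baseline value of the outcome is a prognostic variable and not a confounder, so the phrase does not naturally cover it.

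Four other stronger readings are tempting and not supported:
- **A fixed loss of about 10 points of power.** This holds only near rho 0.5 with the change analysis near 80% power. The article gives neither figure and calls the other research questions less power demanding.
- **A 12-month refill baseline subtracted from a 6-month value.** Records are requested for the year before inclusion, but neither the T0 nor the T1 window is defined. If the windows did differ, the equal-SD formula would not hold exactly. With an assumed T0 SD of 0.85 times the T1 SD and rho 0.5, change variance is 1 + 0.7225 - 0.85 = 0.8725 against 0.75, so 80% power rises to about 86% and not 90%.
- **Bias.** Both analyses are unbiased under randomisation, and type I error is unaffected.
- **All adherence measures.** Monitor output has no value before allocation and no described usual-care counterpart, so baseline adjustment cannot help there.

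**Conclusion.** The point holds as a free improvement and not as an error. On the natural reading, the comparison of refill rate, MAS and MOS-adhere is valid but less efficient than the collected data allow. The size rests on assumptions that the article does not supply. With equal SDs and the change analysis at 80% power, the gain runs from about 13.5 points at rho 0.3 to about 2 points at rho 0.9. It shrinks to about 1 point or less if the true effect is as large as 0.5 SD. If T0 adherence is already a covariate, no power is lost and the text needs only to say so.

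**What to change.** In the Statistical analysis section, replace the sentence on changes in adherence with a repeated measures model of post-baseline adherence: refill rate at T1, T3 and T5, and MAS and MOS-adhere at T1 to T5. Include the T0 value of the same measure as a fixed covariate, plus arm, visit and arm-by-visit. Use the pre-inclusion pharmacy data as the refill baseline. Take the arm difference at T1 as the intervention effect and those at T3 and T5 as the long-term effects. If T0 adherence was already intended as a covariate, state that instead. Leave monitor output outside this model.

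The cost is one sentence and one degree of freedom per model, with no new data, visits or patients.

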### Event adjudication

An independent, blinded, clinical endpoint committee will classify the number of all-cause and cardiac-related deaths.

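### The Kaplan-Meier curves for time to hospitalization leave death outside the endpoint with no stated rule, so by default they would modestly overstate the proportion hospitalized

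*Protocol article*

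**What the plan says.** The Statistical analysis section of the Protocol article states the purpose of the comparison, "To determine whether the time to hospitalization is longer for patients using the MASS device compared with patients in the control group", and then the method, "the log-rank test for comparison of Kaplan-Meier curves will be used". Table 1, under Study endpoints, lists "time to first HF-related hospitalization" among the primary outcomes. Neither place includes death.

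The next sentence of Statistical analysis adds a Cox model for "time to the first event (i.e. hospitalization due to HF or cardiac-related death". Cardiac death is therefore an event in that model, and non-cardiac death is an event in neither analysis.

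Under Event adjudication, a blinded committee "will classify the number of all-cause and cardiac-related deaths", so the deaths will be recorded and classified. The only event rate given is in Statistical power analysis: "Assuming an event rate of 29% (data 2008 and 2009, TweeSteden hospital". The article gives no mortality figure.

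**The concern.** A patient who dies without an admission can no longer be admitted. A Kaplan-Meier curve for one event type has only three options for such a patient: event, still at risk, or censored. With death outside the endpoint and no other rule stated, censoring is the default. The quantity 1-KM then describes a population in which nobody dies, not the share of trial patients who were admitted, and it is too high by an amount that depends on mortality.

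The cohort has systolic heart failure in NYHA class II-III, is aged 50 or over, and is followed for 18 months, so some deaths before a first admission are to be expected. Hospitalization is among the primary endpoints, and readers will take these curves as the proportion admitted in each arm. A comparison of admissions alone also does not show whether a lower rate in one arm goes with more deaths in that arm.

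**Working it through.** The plan states no mortality and no projected hospitalization curve, so there is no figure of its own to reproduce here. The check asks how far 1-KM departs from the true proportion, and then what happens to the log-rank test.

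**Inputs.** True cumulative incidence of hospitalization: 0.29, the event rate in Statistical power analysis. The article gives no time horizon for it; 18 months is assumed. Patients per arm: 200 (Study population and eligibility criteria). Fraction d dying before any admission: assumed 5% to 15%. Cause-specific hazards of admission and death are assumed proportional over time.

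**Size of the overstatement.**
- Total cumulative hazard: H = -ln(1 - 0.29 - d)
- Share due to admission: s = 0.29 / (0.29 + d)
- Kaplan-Meier reading with deaths censored: 1-KM = 1 - exp(-s × H)
- Standard error (SE) of one arm's proportion: sqrt(0.29 × 0.71 / 200) = 3.21 points

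| d | H | s | 1-KM | Excess (points) | Excess / SE |
|---|---|---|---|---|---|
| 5% | 0.4155 | 0.8529 | 29.8% | 0.84 | 0.26 |
| 10% | 0.4943 | 0.7436 | 30.8% | 1.76 | 0.55 |
| 15% | 0.5798 | 0.6591 | 31.8% | 2.76 | 0.86 |

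Outside this range, d = 2% gives an excess of 0.33 points and d = 20% gives 3.87.

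**Effect on the difference between arms.** The SE of the difference is sqrt(2) × 3.21 = 4.54 points. With equal mortality the excess cancels. If both arms truly had 29% admitted and 5% against 15% died first, the curves would differ by 2.76 - 0.84 = 1.92 points, or 1.92 / 4.54 = 0.42 SE. With 5% against 10% the figures are 1.76 - 0.84 = 0.92 points and 0.20 SE.

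**Effect on the log-rank test.** This was simulated with 200 per arm, 4,000 runs per scenario, no device effect on the hazard of admission, and unequal death hazards. The nominal one-sided rate is 2.5%, with a simulation error of sqrt(0.025 × 0.975 / 4000) = 0.25 points.

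- Independent risks, about 8% against 22% dying first: mean z = 0.02, and rejection in favour of the higher-death arm 2.6%. There is no distortion.
- Shared gamma frailty with variance 1, 2 and 4, and about 7-8% against 16-20% dying first: 5.6%, 8.2% and 12.6%.
- The same frailties with a milder imbalance (about 4-5% against 8-9%): 3.9% to 4.8%.
- A log-rank test of hospitalization or any death moved against the higher-death arm in every scenario with unequal death hazards.

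In the independent-risk scenario with 8% against 22% dying first, the Kaplan-Meier readings were 30.2% and 30.3%, while the true cumulative incidences were 28.8% and 26.4%. Cumulative incidence gives the actual share admitted, but it falls where more patients die, so it has to be read beside the death curve.

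**The case against.** The strongest reply has four parts.

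- **Censoring is not stated.** The article does not say that deaths are censored, and a fuller plan could set another rule. This stands as a limit on wording: censoring is what the named estimator does by default, not something the document declares. It does not remove the point, because the article itself fixes the type of curve for an endpoint without death.
- **The log-rank test is legitimate.** Whether the device delays admission can be answered by comparing cause-specific hazards, and the article plans no 18-month proportion by arm. The first half stands, and the test should be kept. On the second, plotted curves will be read as proportions whether or not a number is tabulated.
- **Deaths are partly covered.** The Cox model counts cardiac death, and a blinded committee classifies deaths. This stands, but non-cardiac death remains outside both analyses, and the hospitalization curves use no deaths at all.
- **The size is small and assumed.** This stands too. The excess is below one SE per arm and largely cancels when mortality is similar.

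A reader might infer three stronger things. One is that the cost analysis is biased, since the article says "A cost-benefit analysis will be assessed by means of the TiC-P questionnaire[20] and event rate". But Table 1 takes rehospitalisations and treatment codes from medical records, which are actual admissions, and nothing says that the event rate is read from 1-KM. Another is that the arm with more early deaths will look better. The simulation shows this only when death and admission share a common risk, which is plausible in heart failure but is an assumption. A third is that Gray's test should replace the log-rank test. That test compares cumulative incidence, which itself falls with more deaths, so it would not cure the problem.

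**Conclusion.** The point holds in a limited form. As written, the Kaplan-Meier curves would by default censor patients who die unadmitted and overstate the proportion hospitalized. The excess is about 0.8 to 2.8 points per arm if 5% to 15% die first. That range is assumed, as are the use of 29% as the 18-month incidence and proportional cause-specific hazards. The effect on the difference between arms is smaller and close to zero when mortality is similar.

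The log-rank test is valid as a cause-specific comparison. It could favour an arm with more deaths only if the risks of death and admission are correlated, and the effect is modest unless mortality differs strongly. The Cox model closes the gap for cardiac death but not for non-cardiac death. The documents do not support a claim of a biased cost analysis or of an invalid test. The change is still worth making, because the direction of the error in the curves is known, the deaths are already being classified, and the repair is cheap.

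**What to change.** - In Statistical analysis, replace the Kaplan-Meier curves for hospitalization with Aalen-Johansen cumulative incidence curves that treat death without admission as a competing event.
- Keep the log-rank test and label it as a comparison of cause-specific hazards.
- Keep the Cox model and state that non-cardiac death is censored in it.
- Report all-cause death by arm beside these results.
- Add a sensitivity analysis of time to hospitalization or death from any cause.

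This needs a few sentences of wording and standard software. It needs no new data and no change to the sample size or conduct. The small downside is one extra curve and one extra analysis to report.
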